### Outcome measures

#### Primary outcomes.

The primary outcomes of this study include skeletal muscle mass, muscle strength, and physical performance. Skeletal muscle mass will be measured using dual-energy X-ray absorptiometry (DXA) through whole-body scanning. Total appendicular skeletal muscle mass will be calculated by summing the values from all four limbs. A threshold of < 7.0 kg for men and < 5.4 kg for women will be used to identify sarcopenia.

Muscle strength will be assessed using a calibrated handgrip dynamometer (5030JI, Jamar, IL, USA). Participants will be instructed to squeeze the device maximally for a few seconds while holding it at a 90° elbow angle by their side. Three measurements will be taken bilaterally, and the highest value will be recorded. According to the AWGS 2019 criteria, handgrip strength < 28 kg for men and < 18 kg for women indicates low muscle strength. Physical performance will be evaluated via the 6-meter gait speed test, with a cutoff of < 1.0 m/s used to define poor performance, based on the AWGS 2019 recommendations.

#### Secondary outcomes.

IGF-1 concentrations will be assessed *via* an enzyme-linked immunosorbent assay (ELISA) kit (IGF-1 600 ELISA; DRG, Germany). Blood will be collected from the antecubital vein in a fasting state in serum separator tubes, centrifuged for 15 minutes at 3000 × g and 4°C to harvest serum, which will be stored at −80°C for biochemical analysis [57].

The PI3K/AKT signaling pathway and FOXO3 protein activity will be assessed using immunoblotting (Western blot) and cell isolation assay on specimens obtained via muscle biopsy. Muscle biopsies will be collected at three time points: baseline (pre-intervention), 12 weeks (post-intervention), and 24 weeks (follow-up), enabling longitudinal analysis of the IGF-1/PI3K/AKT/FOXO3 axis. Although more frequent sampling could provide a finer-grained understanding of molecular responses, ethical and practical concerns regarding repeated invasive procedures in older adults limit the feasibility of acute or intra-intervention biopsies in this study. The percutaneous muscle biopsy technique will be employed for lateral femoral muscle biopsy. Briefly, after 2–3 mL of 1% dimethocaine local anesthesia, aspiration will be performed. Then, about 50 mg of muscle tissue lacking blood vessels and connective tissues will be dissected. The samples will be immediately placed in cryotubes, frozen in liquid nitrogen, and stored at −80°C [58].

Then, the protein content will be evaluated *via* the bicinchoninic acid assay (BCA) method (Pierce, Appleton, WI, USA). Subsequently, equal amounts of protein will be subjected to 12% SDS-PAGE gel electrophoresis and transferred onto PVDF membranes, which will then be treated at 4°C with the primary antibodies against PI3k (ab140307,1:1000, Abcam, UK), Akt (SAB4500797, 1:1000, Sigma, USA), Akt (phospho T308) (ab38449, 1:1000, Abcam, UK), and FOXO3 (SAB2107951, 1:1000, Sigma, USA) overnight. Next, the membranes will be flushed with phosphate-buffered saline with tween (PBST), probed with the HRP-linked specific goat anti-rabbit IgG secondary antibody (ab150077, 1:3000, Abcam, UK) for 2 h at ambient temperature, and then washed thrice with PBST. The bands will subsequently be quantified *via* the Image Lab system (Bio-Rad, Shanghai, China) [59,60]. The above analyses will be performed in the Sports Medicine Key Laboratory of Sichuan Province.

A timed-up-and-go test will be performed, during which the time it takes for participants to get up from the chair, walk 3 meters, turn around, go back to the chair, and then sit down will be recorded.

The validated Chinese version of the 36-item short form health survey will be employed to elucidate health-related quality of life. This instrument will evaluate both physical and mental components, with the total score reflecting overall quality of life, with higher values corresponding to better outcomes. [61]

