**Method:**

This prospective randomized controlled trial will be conducted among 96 participants, aged between 65 and 80 years. In participants, sarcopenia diagnosis will be confirmed based on the Asian Working Group for Sarcopenia criteria, and participants will be randomized into either control, RT, VT, or RVT (combined RT and VT) groups. The intervention will last 12 weeks, with assessments performed at baseline, 12 weeks (after intervention), and 24 weeks (follow-up). The primary outcomes will include skeletal muscle mass, handgrip strength, and gait speed. Secondary outcomes comprise IGF-1 concentrations, PI3K/AKT and FOXO3 protein activity, quality of life, and timed-up-and-go test performance assessments.

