Sarcopenia has been linked to reduced levels of anabolic hormones, specifically insulin-like growth factor 1 (IGF-1), among individuals aged 60 years and above [12]. Forkhead box protein O3 (FOXO3) is a downstream component of the IGF-1 signaling pathway and is crucial for catabolic/anabolic protein homeostasis and protein breakdown within the musculoskeletal system [13]. IGF-1 activates phosphatidylinositol 3 kinase (PI3K) by binding to its receptor, which catalyzes the conversion of phosphatidylinositol-4,5-bisphosphate (PIP2), a membrane-bound molecule, to phosphatidylinositol-3,4,5-trisphosphate (PIP3), which recruits and activates protein kinase B (AKT). This, in turn, phosphorylates FOXO3 and inhibits its nuclear translocation and transcriptional activity [14]. In the anabolic state, this process decreases the expression of FOXO3’s downstream target genes (e.g., MuRF-1 and Atrogin-1 act as ubiquitin ligases and induce proteasomal degradation) and inhibits muscle protein degradation [15]. When IGF-1 signaling is diminished (e.g., owing to aging or stress), AKT activity decreases and FOXO3 dephosphorylates and enters the nucleus, stimulating an increase in MuRF-1 and Atrogin-1 levels, as well as promoting muscle atrophy *via* the ubiquitin-proteasome pathway [16–18]. Thus, a lower IGF-1 level can lead to a higher FOXO3 activity via the PI3K/AKT pathway, causing protein degradation and skeletal muscle atrophy [19], thereby resulting in the onset of sarcopenia in older adults. Among the various regulatory genes in the musculoskeletal system, FOXO3 is crucial; therefore, its inhibition might be a potential strategy for treating muscle atrophy and sarcopenia [12]. On the basis of the above evidence, it is crucial to examine the influence of different sarcopenia treatment strategies on the IGF-1/PI3K/AKT/FOXO3 pathway.

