In terms of the cell signaling pathways, animal studies have shown IGF-1 pathway activation via VT [34]. Increased IGF-1 levels and improved muscle mass were also observed in sarcopenic patients after RT [35]. However, another study found no increase in inactivated FOXO3 in older women after 12 weeks of RT, implying limited benefits of RT in these women [36]. Preclinical studies have further demonstrated that vibration stimuli can promote muscle protein synthesis via mechanical loading–induced IGF-1 expression. For instance, Li et al. [34] reported that VT activated the PI3K/AKT/mTOR pathway and suppressed muscle atrophy in aged mice. Human studies have also reported increased serum IGF-1 levels following VT, suggesting systemic anabolic responses [28]. The proposed mechanism in this study is that VT enhances neuromuscular activation and mechanosensitive stimulation, which upregulates IGF-1 production. This in turn activates the PI3K/AKT signaling cascade, leading to phosphorylation of FOXO3 and reduced expression of its downstream catabolic targets, MuRF-1 and Atrogin-1. Thus, VT may shift the muscle environment toward an anabolic state through modulation of the IGF-1/PI3K/AKT/FOXO3 axis. This forms the central mechanistic hypothesis of the present protocol.

Sex-specific differences in sarcopenia are well recognized. A recent study has shown that women tend to experience a more rapid decline in muscle strength relative to muscle mass, whereas men are more likely to exhibit significant reductions in muscle mass with aging [37]. These disparities may be influenced by differences in hormonal status (e.g., estrogen vs. testosterone), muscle fiber composition, and neuromuscular control mechanisms [38]. Additionally, evidence suggests that men and women may respond differently to exercise interventions such as resistance and vibration training [39,40]. Therefore, sex-specific considerations are essential when designing sarcopenia-related interventions and interpreting outcomes.

In this study, we investigate the impact of RT combined with VT on the IGF-1/PI3K/AKT/FOXO3 axis in patients with sarcopenia. Using a single-blind randomized controlled trial, we will assess whether this combined exercise therapy exerts significant molecular and functional effects, while also exploring potential differences in treatment response between sexes.

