## Methods and analysis

### Study design and grouping

This randomized controlled trial will identify the effects of RT combined with VT on the IGF-1/PI3K/AKT/FOXO3 axis in a population with sarcopenia. Participants will be screened for sarcopenia, as defined by the AWGS in 2019, and recruited based on eligibility criteria. Fig 1 summarizes the participant’s enrollment process, interventions, and assessment schedule. Once informed consent is received, the participants will be randomly categorized into (1) control, (2) RT, (3) VT, and (4) combined RT and VT (RVT) groups. Intervention will last 12 weeks, with data collection and assessments at baseline, 12-week (after intervention), and 24-week (follow-up). The 12-week intervention duration was selected based on existing literature indicating that this time frame is sufficient to induce meaningful improvements in muscle mass, muscle strength, and molecular signaling among older adults. Prior studies on resistance and vibration training for sarcopenia typically range between 8–12 weeks, with 12 weeks allowing both early neural adaptation and later-stage hypertrophy to manifest [41–43]. The 24-week time point (i.e., 12weeks post-intervention) was included to evaluate the sustainability of training-induced benefits. Similar follow-up durations have been adopted in previous sarcopenia trials to assess the persistence or decay of functional gains after supervised training ends [44]. Muscle strength, mass, physical performance, FOXO3 protein expression levels, and quality of life will be assessed in all participants. Fig 2 depicts the study design, and S1 File contains the SPIRIT checklist.

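### The secondary outcome FOXO3 activity is not matched by the listed assays, so the FOXO3 step of the mechanistic hypothesis is not shown to be testable

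*Protocol article*

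**What the plan says.** The outcome is named in three places in the protocol article, and not in the same way.

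- Abstract, Method: "Secondary outcomes comprise IGF-1 concentrations, PI3K/AKT and FOXO3 protein activity".
- Secondary outcomes: "The PI3K/AKT signaling pathway and FOXO3 protein activity will be assessed using immunoblotting (Western blot) and cell isolation assay".
- Study design and grouping lists it as "FOXO3 protein expression levels".

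The Introduction explains what activity means for this protein. Activated AKT "phosphorylates FOXO3 and inhibits its nuclear translocation and transcriptional activity". When AKT activity falls, the reverse happens: FOXO3 loses its phosphate, moves into the nucleus and raises MuRF-1 and Atrogin-1. The proposed action of vibration training runs through the same step, "leading to phosphorylation of FOXO3 and reduced expression of its downstream catabolic targets, MuRF-1 and Atrogin-1", and the Introduction calls this chain the central mechanistic hypothesis.

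The blot has four primary antibodies. PI3K and Akt come first, and the list then ends: "Akt (phospho T308) (ab38449, 1:1000, Abcam, UK), and FOXO3 (SAB2107951, 1:1000, Sigma, USA) overnight". Each is given with catalogue number, dilution and supplier. Equal protein loads are run on the gel. The cell isolation assay appears once, by name only.

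**The concern.** The document defines FOXO3 activity by phosphorylation state and location in the cell, but the assays it lists appear to yield an amount. These are different quantities. If AKT phosphorylates more FOXO3 without changing how much is present, a blot of the whole protein stays flat while the protein becomes less active.

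A flat result could then be taken as no effect on FOXO3, and a shift in amount could be taken as a shift in activity. This matters because the stated purpose is the effect of training on the IGF-1/PI3K/AKT/FOXO3 axis, and FOXO3 is the end of that axis. The tissue comes from muscle biopsies at three visits in older adults, at most 96 × 3 = 288 if nobody drops out. The article itself cites ethical limits on taking more.

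**Working it through.** There is no figure to reproduce. The check sets each link of the hypothesis (Introduction) beside the assay listed for it (Secondary outcomes).

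| Link in the hypothesis | Assay listed | Status |
|---|---|---|
| 1. IGF-1 rises | Serum ELISA | Measured |
| 2. PI3K is engaged | One PI3K blot, no activation label | Measured as one blot |
| 3. AKT is activated | Akt and phospho-Akt (T308) blots | Measured, phospho and unlabelled forms |
| 4. FOXO3 is phosphorylated | One FOXO3 blot, no phospho label | No listed antibody is labelled for it |
| 5. FOXO3 is kept out of the nucleus | No fractionation described; cell isolation assay undefined | Not shown |
| 6. MuRF-1 and Atrogin-1 fall | None | Not measured, and not declared as outcomes |

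Links 1 to 3 are covered. Links 4 and 5 are the ones the Introduction uses to say whether FOXO3 is active, and neither has a described readout. Link 6 is a downstream consequence.

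Why amount cannot stand in for activity: let T be total FOXO3, P the phosphorylated part and s = P/T the phosphorylated share. On the Introduction's account the part free to act is

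U = T − P = T × (1 − s).

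A blot for total protein estimates T alone.

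- If T is unchanged, s may still rise or fall, and U moves the opposite way. The blot shows nothing.
- If T rises while (1 − s) falls by a larger factor, U falls. The blot moves in the wrong direction.

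So T determines neither the size nor the sign of a change in U. A phospho-FOXO3 blot beside a total-FOXO3 blot gives s up to a scale constant. That is the information missing for FOXO3 and already available for Akt.

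The Introduction's own precedent points the same way. The earlier trial of 12 weeks of resistance training in older women is reported there in terms of the inactivated form of FOXO3, not its amount.

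The naming was compared last. Two places say activity and one says expression levels. The antibody list fits the second term.

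**The case against.** **An article condenses, and laboratory detail belongs in the full protocol or in the cited methods papers.** This has force for the cell isolation assay. If that assay separates nuclear from cytoplasmic protein, link 5 could be covered, so the document does not support saying that nuclear entry goes unobserved; it only fails to show that it is observed. The objection has less force for the antibodies. They are listed with catalogue numbers and dilutions, and a phospho-site is given for Akt. An unlabelled FOXO3 entry beside it is not explained by brevity. Nuclear fractionation would also leave phosphorylation unmeasured.

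**Total FOXO3 is an inference.** Correct. The word is not in the document, and the specificity of the catalogue number cannot be checked from it. If the antibody is in fact phospho-specific, the label needs correcting and the total form needed for a ratio is then missing. Action is needed either way.

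**The central hypothesis is still largely testable.** A reader might infer that the whole hypothesis cannot be tested. The document does not support that. IGF-1 is measured, and so is phospho-Akt, which is the step the Introduction places immediately before FOXO3 phosphorylation.

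**MuRF-1 and Atrogin-1 are not promised.** A reader might count their absence as an error. It is not one. The stated objective stops at FOXO3, and neither protein is listed as an outcome.

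**Misreading is a prediction.** Also fair. No rule for interpreting a flat FOXO3 result is stated. The biopsies are not wasted either, since they also serve the PI3K and Akt blots. The Discussion concedes in general terms that not every adaptation will be captured, but its limitations deal with biopsy timing and do not mention this gap.

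**Conclusion.** The point holds for the FOXO3 step of a secondary outcome, and no further. The protocol promises FOXO3 activity, ties activity to phosphorylation and nuclear location, and lists no assay shown to measure either. Elsewhere it calls the same outcome expression. Followed as written, the plan would report protein amount under the name of activity.

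The size is structural, not numerical: of the two links that define FOXO3 activity in the Introduction, none has a described readout, while the links from IGF-1 to phospho-Akt do. The primary outcomes, the sample size and the tests of IGF-1 and phospho-Akt are unaffected.

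The conclusion rests on two assumptions: that the unlabelled FOXO3 antibody detects total protein, and that the cell isolation assay does not measure nuclear FOXO3. If the second is wrong, nuclear location would be covered but phosphorylation would not.

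**What to change.** Preferred: add a phospho-FOXO3 antibody to the blots, run it on the same lysates as the existing FOXO3 antibody, and define FOXO3 activity as the phospho/total FOXO3 ratio, with a higher ratio meaning less activity. Confirm that the listed FOXO3 antibody detects total protein. State in one sentence what the cell isolation assay measures, and in particular whether it measures nuclear FOXO3. Settle this before the blots are quantified.

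The cost is one more antibody and some lysate, with no extra biopsy or visit. About 50 mg of muscle is taken per biopsy and stored at −80°C. The article gives no lysate yield, so the laboratory should check that there is enough.

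Alternative: rename the outcome *FOXO3 protein expression* in the Abstract and under Secondary outcomes, which brings both into line with Study design and grouping, and draw no conclusion about FOXO3 activity. This costs nothing in laboratory work but gives up the FOXO3 step of the hypothesis.

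Measuring MuRF-1 and Atrogin-1 is optional under either route.

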### Statistical analysis

IBM SPSS v.20.0 will be utilized to analyze all the data. The primary outcomes will be assessed using two-way repeated-measures analysis of variance (ANOVA), with factors including time (baseline, 12 weeks, 24 weeks) and group (control, RT, VT, RVT). This approach was selected to allow direct estimation of group-by-time effects for predefined primary endpoints under a balanced design. Holm–Bonferroni adjustments will be applied for post-hoc pairwise comparisons. Missing data will be imputed via multiple imputation. Sex, along with baseline IGF-1, age, and muscle mass, will be included as covariates in analysis of covariance (ANCOVA) models to adjust for potential confounding effects. Effect sizes (partial η^2^ for ANOVA; for pairwise comparisons, the Cohen’s d with 95% confidence intervals were employed) will be categorized as small (η^2^ ≥ 0.01, d ≥ 0.2), medium (η^2^ ≥ 0.06, d ≥ 0.5), or large (η^2^ ≥ 0.14, d ≥ 0.8), accompanied by exact p-values. The 95% confidence intervals for Cohen’s d and model-based estimates will be calculated using either model-derived standard errors or the bias-corrected and accelerated (BCa) bootstrap method with 1,000 resamples, depending on distributional assumptions. To better accommodate repeated measures and potential within-subject correlations in secondary longitudinal outcomes, linear mixed-effects models will be used, incorporating random intercepts for participants and fixed effects for time, group, and their interaction. In addition, exploratory subgroup analyses stratified by sex will be conducted to evaluate potential sex-specific intervention effects. Subgroup interaction terms will be tested where appropriate, with p < 0.10 considered indicative of potential moderation. Statistical significance will be defined as p < 0.05 for all primary tests. Although the current sample size is not specifically powered to detect sex-based interaction effects, these exploratory analyses will inform the design of future sex-specific trials. All analyses will follow the intention-to-treat (ITT) principle. All randomized participants will be analyzed according to their assigned groups, regardless of protocol adherence or study completion status.

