### Sample size determination

The required sample size was calculated using G*Power (version 3.1.9.7, Germany) for a two-way repeated-measures ANOVA (within-between interaction), with a significance level of α = 0.05, power (1–β) = 0.80, and four intervention groups (Control, RT, VT, RVT). The effect size was set to f = 0.40 (partial η^2^ = 0.14), which reflects a moderate-to-large effect based on prior studies assessing changes in IGF-1 expression and physical function following resistance and vibration training in older adults. The primary endpoint for power estimation was the change from baseline to 12 weeks, representing the completion of the supervised intervention. The 24-week point is considered a follow-up to assess sustainability but was not included in the power calculation. Considering a 20% dropout rate, the minimum required sample size was estimated at 73 participants [45]. Therefore, we plan to recruit 96 individuals (24 per group) to ensure adequate statistical power. In view of multiple primary outcomes and six pairwise comparisons among four groups, Holm–Bonferroni correction will be applied to adjust for potential inflation of type I error. Additionally, the hypothesis is based on additive rather than synergistic effects between RT and VT. Hence, interaction effects were not included in the sample size model but will be explored post hoc.

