### Exclusion criteria

The exclusion parameters included individuals with: 1) uncontrolled hypertension, hyperlipidemia, or diabetes mellitus; 2) untreated gallstones, kidney stones, or infectious diseases; 3) pathological bone diseases or chronic inflammatory diseases (e.g., rheumatoid arthritis); 4) any disorders that limit the ability to complete the required exercises in the study; 5) cardiovascular disease requiring a pacemaker or having a malignant tumor; 6) acute fractures or severe osteoarthritis; 7) current use of medications known to affect muscle metabolism or hormonal balance, including but not limited to systemic corticosteroids, anabolic steroids, or hormone replacement therapy. Additionally, all participants’ current use of medications for cardiovascular or metabolic conditions (e.g., beta-blockers, statins, insulin sensitizers) will be documented at baseline. If imbalances between groups are identified, these variables will be considered as covariates in the statistical analysis; 8) current or recent (within the past 3 months) use of nutritional supplements that may affect muscle metabolism or sarcopenia progression, such as protein powders, amino acids, vitamin D, or calcium supplements.

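### The trial is sized on the 12-week change, but the primary outcomes are tested by a three-time-point group-by-time interaction that a difference at week 24 alone can make significant

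*Protocol article*

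**What the plan says.** Sample size determination in the protocol article is explicit about the target: "The primary endpoint for power estimation was the change from baseline to 12 weeks, representing the completion of the supervised intervention". On the last visit it says: "The 24-week point is considered a follow-up to assess sustainability but was not included in the power calculation". The sizing method is a "two-way repeated-measures ANOVA (within-between interaction), with a significance level of α = 0.05, power (1–β) = 0.80, and four intervention groups".

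Statistical analysis then assigns the primary outcomes (muscle mass, handgrip strength, gait speed) to a "two-way repeated-measures analysis of variance (ANOVA), with factors including time (baseline, 12 weeks, 24 weeks) and group (control, RT, VT, RVT"), with the group-by-time effects as its aim. Pairwise comparisons follow with a Holm–Bonferroni adjustment, but no time point is given for them.

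On covariates the same section says: "Sex, along with baseline IGF-1, age, and muscle mass, will be included as covariates in analysis of covariance (ANCOVA) models". Baseline handgrip and baseline gait speed are not on that list. The Exclusion criteria section adds a rule for medications recorded at baseline: "If imbalances between groups are identified, these variables will be considered as covariates in the statistical analysis".

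**The concern.** The two sections describe different tests. With two time points and four groups the interaction has 3 degrees of freedom and asks one question: do the groups differ in their change to week 12? With three time points it has 6 degrees of freedom and asks whether the group profiles differ anywhere across baseline, week 12 and week 24. Week 24 comes 12 weeks after the supervised programme ends.

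This has two consequences. A significant primary result need not mean that the groups differed at week 12, which is the claim the trial was sized to support. A non-significant one may partly reflect gains fading after training stopped. In addition, handgrip and gait speed are measured at baseline but not used as covariates for themselves, so precision already paid for is left unused. The medication rule makes the adjusted model depend on which imbalances are found.

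**Working it through.** **Inputs from the protocol article.** Four groups, α = 0.05, power 0.80, f = 0.40, 20% dropout, stated minimum 73, planned 96 (24 per group). After 20% dropout, 96 × 0.80 = 76.8, taken as 77.

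**Assumptions, because the article gives no figure.** The within-person correlation ρ is taken from 0.5 to 0.9, equal between visits. The share r of the 12-week effect kept at week 24 is taken from 0 to 1. f = 0.40 is read as the effect on the 12-week change.

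**Step 1: reproduce the stated 73.** For the two-time-point interaction, which is the same as a one-way ANOVA on the change, λ = N f² with df 3 and N − 4. At N = 73, λ = 73 × 0.16 = 11.68 and power is 0.805; at N = 72 it is 0.799. So 73 is the smallest N for the two-time-point test, before any dropout (73 / 0.80 gives 92, which 96 covers). The three-time-point variants tried do not give 73: 46 or 50 under two common effect-size conventions, 18 under a third with ρ = 0.5. The sizing therefore belongs to the 12-week test.

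**Step 2: power of the planned three-time-point interaction.** With profile (0, 1, r) over the three visits and equal correlations, λ = 2 N f² × SS, where SS = 1 + r² − (1 + r)²/3, with df 6 and 2(N − 4). SS is 0.667 for r = 0 or 1, 0.542 for r = 0.25 or 0.75, and 0.500 for r = 0.5. The factor 2(1 − ρ) that links the change variance to the single-visit variance cancels, so ρ drops out.

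| Share kept at week 24 | N = 77 | N = 96 |
|---|---|---|
| none or all | 0.86 | 0.94 |
| a quarter or three quarters | 0.77 | 0.87 |
| half | 0.73 | 0.84 |
| 12-week change test, for comparison | 0.83 | 0.91 |

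Equal correlation favours the planned test. In a simulation (2,000 runs per scenario) with first-order autoregressive correlation 0.8, N = 76 and a Greenhouse–Geisser correction, it had 0.77, 0.55 and 0.71 with none, half and all of the effect kept, against about 0.82 for the change test.

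**Step 3: does the planned test answer the 12-week question?** Set the groups equal at week 12 and put the same-sized difference at week 24 only. The profile is then (0, 0, 1) and SS = 0.667, so the planned test rejects with probability 0.86 at N = 77 and 0.94 at N = 96. By simulation it rejected in 84–87% of runs at N = 76 and 93–95% at N = 96 under equal correlation, and in 69–84% across both sizes under the autoregressive pattern. A week-12 test rejects in about 5%.

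**Step 4: own-baseline adjustment at week 12.** The residual variance is 1 − ρ² instead of 2(1 − ρ), so λ = N f² × 2/(1 + ρ), with df 3 and N − 5.

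| ρ | λ at N = 77 | Power, N = 77 | Power, N = 96 |
|---|---|---|---|
| 0.5 | 16.43 | 0.93 | 0.97 |
| 0.7 | 14.49 | 0.89 | 0.95 |
| 0.8 | 13.69 | 0.87 | 0.94 |
| 0.9 | 12.97 | 0.85 | 0.93 |

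All figures in these steps are for one omnibus test of one outcome at α = 0.05, before any Holm–Bonferroni adjustment.

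**The case against.** A reader might go further than the document allows in four ways.

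- **That the planned test simply loses power.** It does not in general. Under equal correlation it is slightly ahead of the change test when all or none of the gain is kept, and with all 96 analysed it stays at 0.84 or above. The loss needs partial retention or a less favourable correlation pattern, and the article states neither.
- **That handgrip and gait speed are never adjusted for baseline.** Baseline is a level of the time factor, so the interaction already compares changes from each outcome's own baseline. What is absent is covariate adjustment. In a randomised trial that is a matter of precision, and it is worth little at high correlation: 0.85 against 0.83 at ρ = 0.9.
- **That two rival primary models leave the choice open.** Only the repeated-measures ANOVA is attached to the primary outcomes; the ANCOVA is brought in for adjustment and never called primary. How its covariates enter is detail a condensed article may leave to an analysis plan. The medication trigger is baseline imbalance, not outcome results.
- **That keeping the mixed model for secondary outcomes discards data.** The section says "in secondary longitudinal outcomes, linear mixed-effects models will be used", but it also plans multiple imputation and intention-to-treat analysis of everyone randomised.

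The omnibus test does include the week-12 difference, and pairwise comparisons follow it. But their time point is unstated, so they do not restore the 12-week question. None of these arguments removes the mismatch: both sections are explicit and they disagree.

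**Conclusion.** The point holds as a mismatch between the endpoint that was powered and the test that decides. It does not rest on any assumption about power: the stated 73 reproduces only as the two-time-point test, and the planned interaction rejects with probability of about 0.86 (N = 77) or 0.94 (N = 96), under equal correlation, when an effect of the assumed size exists at week 24 only.

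The effect on power is conditional. At N = 77 it runs from 0.10 below the change test (0.73 against 0.83, half kept) to 0.03 above it (0.86, all or none kept). At N = 96 it runs from 0.07 below to 0.03 above. Own-baseline adjustment at week 12 would add 0.02 to 0.10 over the change test at N = 77 across correlations of 0.9 down to 0.5. These figures rest on f = 0.40 for the 12-week change, equal correlations and a single test at 0.05. The covariate points are improvements in precision and prespecification, secondary to the time-point mismatch.

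**What to change.** 1. For each primary outcome, name the between-group comparison at week 12 as the primary test, from a model with that outcome's own baseline value plus the covariates already planned (sex, age, baseline IGF-1, muscle mass).
2. Keep the planned Holm–Bonferroni correction over the primary outcomes and the six pairwise comparisons, and say that these comparisons are made at week 12.
3. Report the week-24 comparisons as secondary, as evidence on whether gains last.
4. Replace the imbalance-triggered medication covariates with covariates fixed in advance, or move them to a sensitivity analysis.

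This costs wording only: no extra participants, visits or measurements. The article says enrolment is continuing, so the change can be made and dated before the analysis. The price is that week-24 data no longer contribute to the primary claim, including in the cases (all or none of the gain kept, equal correlation) where they would have helped slightly relative to an unadjusted change test.
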